## Abstract

**Background:**

The prevalence of prediabetes is increasing worldwide. Unfortunately, prediabetes is related to non-communicable diseases. A high risk of developing type 2 diabetes mellitus (T2DM) is reported in people with prediabetes. Curcumin, a polyphenol, might lead to its therapeutic role in obesity and some obesity-related metabolic diseases. Zinc is a trace element that plays a key role in the synthesis and action of insulin, carbohydrate metabolism, and decreasing inflammation. There has been no clinical trial of zinc and curcumin co-supplementation in patients with prediabetes. In previous studies, the single administration of zinc or curcumin has not been conducted on many of the studied markers in prediabetic patients.

**Methods:**

The purpose of this randomized double-blind placebo-controlled clinical trial is to investigate the effect of curcumin and zinc co-supplementation on glycemic measurements, lipid profiles, and inflammatory and antioxidant biomarkers among 84 prediabetic patients with body mass index (BMI) between 25 and 35. Also, liver enzyme, serum zinc, urine zinc, blood pressure, anthropometric parameters, quality of life, adherence to co-supplementation, the side effects of co-supplementation, physical activity, and dietary intake will be assessed. Women or men (18–50 years old for men and 18 years to before menopause for women) will be followed for 3 months (90 days). This study will be conducted at Yazd Diabetes Research Clinic, Shahid Sadoughi University of Medical Sciences.

**Discussion:**

A diet rich in antioxidants, polyphenols, and phytochemicals has been shown to have a beneficial role in prediabetes. According to the beneficial properties of curcumin or zinc and inadequate evidence, RCTs are needed to assess the effect of curcumin and zinc co-supplementation in native prediabetes patients. We hope the results of the present trial, negative or positive, fill this gap in the literature and facilitate the approach for a much larger, multi-center clinical trial. In conclusion, a synergic effect of co-supplementation along with a weight-loss diet may delay the progression to type 2 diabetes mellitus.

**Trial registration:**

Iranian Registry of Clinical Trials (IRCT) IRCT20190902044671N1. Registered on 11 October 2019

## Introduction

### Background and rationale

Prediabetes or intermediate hyperglycemia [1] is the state referred to as impaired fasting glucose (IFG), impaired glucose tolerance (IGT), or glycated hemoglobin A1C (HbA1C) of 5.7 to 6.4% (39–47 mmol/mol). There is a difference in terms of the diagnostic criteria for illustrating a prediabetes state between the American Diabetes Association (ADA) [2], International Diabetes Federation (IDF) [3], and World Health Organization (WHO) [4] (Supplementary Material, Table S1). The prevalence of prediabetes is increasing worldwide [5].

Unfortunately, prediabetes is related to non-communicable diseases (the different types of obesity, dyslipidemia, and hypertension) [6]. A high risk of developing type 2 diabetes mellitus (T2DM) is reported in people with prediabetes [7]. However, it is preventable [8] by lifestyle interventions [9] (such as weight-loss strategies using dietary changes and/or physical activity [10]). The beneficial effects of a diet rich in antioxidants [11], polyphenols [12], and phytochemicals [13] have been shown in many studies.

Turmeric (*Curcuma longa*) is a plant-derived spice related to the ginger family (Zingiberaceae) with medicinal properties. The largest producer of turmeric is India. The bioactive yellow molecules in turmeric are called curcuminoids [14] that consist of curcumin (diferuloylmethane) (CUR), demethoxycurcumin (DMC), and bisdemethoxycurcumin (BMC) [15]. Curcuminoids are generally recognized as safe (GRAS) according to the US Food and Drug Administration (FDA) [16]. Also, a maximum single oral dose (12 g/day) of curcuminoids is well tolerated [17]. In addition, the 6-month intervention of curcumin shows only slight adverse effects [18]. Curcumin, a polyphenol [19], can improve metabolic syndrome (MeS) [20], diabetes, antioxidant capacity [21], cancer [15], and arthritis [22].

Curcumin modulates the several cellular transduction pathways and molecular targets (advanced glycation end-product (AGE)-mediated induction of the receptor for AGE gene expression, de novo synthesis of glutathione, PPARγ activity, NF-kB, STAT-3, Nrf2, TNF-α, IL-1β, resistin and leptin, adiponectin, etc.) which might lead to its therapeutic role in obesity and some obesity-related metabolic diseases such as T2DM [23–25]. The effect of curcumin alone or combined with nutraceuticals in prediabetic patients was shown in three trials [26–28]. In four studies, it was assessed in the patients with MeS (prediabetes, pre-hypertension, or dyslipidemia) [29, 30] and non-alcoholic fatty liver disease (NAFLD) [31] or prediabetic or controlled T2DM [32].

Zinc is a trace element that plays a key role in more than 300 enzymes [33] such as antioxidant enzymes, synthesis and action of insulin, carbohydrate metabolism [34], and decreasing inflammation [35]. Zinc levels improve the glycemic status, lipid parameters [36] (total cholesterol (TC), serum low-density lipoprotein cholesterol (LDL-C), and triglycerides (TG)) [37], and blood pressure (BP) [36]. Some complications of diabetes may be related to oxidative stress, and zinc can be an essential element in the cellular antioxidative defense [34]. Also, there is a high concentration of zinc in human pancreatic beta cells [38]. The effect of zinc alone or combined was assessed in prediabetic patients by two trials [39, 40], and it was investigated on MeS only in one trial [41].

The characterizations of the previous studies, which are related to the title of this research, are shown in Table S2 (Supplementary Material).

Both zinc and curcumin have antioxidant properties [21, 34]. Co-supplementation of curcumin and zinc in patients with prediabetes is not yet studied. Also, in previous studies, the effect of a single administration of zinc or curcumin has not been evaluated simultaneously on many of the studied markers in patients with prediabetes. These supplementations are remarkably free of toxicity [19, 42], and they have been used as an available and inexpensive food condiment for human consumption. It is proposed that their usage along with a weight-loss diet may show synergistic effects in prediabetes. So, this double-blind, randomized placebo-controlled clinical trial (randomized clinical trial (RCT)) will start with the following objectives and hypothesis.

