### Sample size

The sample size was determined based on the ability to detect a mean effect of FPG between the supplement and placebo groups for each supplement (curcumin or zinc), separately.

By using the following formula, the maximum sample size for curcumin group based on the trial by Chuengsamarn et al. [26] and zinc group based on the trial by Ranasinghe et al. [40] was determined to be 8 ($$ {\overline{X}}_1 $$ = 3.64, $$ {\overline{X}}_2 $$ = − 7.54, *S*_1_ = 8.17, and *S*_2_ = 7) and 19 ($$ {\overline{X}}_1 $$ = + 16, $$ {\overline{X}}_2 $$ = + 3, *S*_1_ = 12.8, and *S*_2_ = 15.3), respectively (*α* = 0.05, significance; *β* = 0.2, power). Then, the maximum sample size was considered as the final sample size, which is sufficient to evaluate the main effects. According to an expected 10% loss at follow-up, 84 subjects (21 participants in each group) will be recruited, finally.

$$ {n}_1=\frac{\left({S}_1^2+{S}_2^2\right){\left({Z}_{1-\frac{\alpha }{2}}+{Z}_{1-\beta}\right)}^2}{{\left({\overline{X}}_1-{\overline{X}}_2\right)}^2} $$

In the formula above, *S*^2^ and $$ \overline{X} $$ show the variance and the mean effect for FBS in the placebo and treatment groups, respectively. Also, for a more accurate calculation of the sample size, the WinPepi statistical program (version 11.4: Abramson, 2011) was performed.

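### Synergy is proposed in the rationale and the abstract, but the stated analysis has no curcumin-by-zinc interaction and the sample size was not set for one

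*Protocol article*

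**What the plan says.** Under Background and rationale, the protocol article gives the reason for combining the supplements: "It is proposed that their usage along with a weight-loss diet may show synergistic effects in prediabetes". The next sentence introduces the trial as following from this. The Discussion paragraph of the abstract ends by saying that "a synergic effect of co-supplementation along with a weight-loss diet may delay the progression to type 2 diabetes mellitus".

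Study design sets out a 2 × 2 factorial with four equal groups: curcumin, zinc, both, and double placebo, followed for 90 days. Sample size rests on "the ability to detect a mean effect of FPG between the supplement and placebo groups for each supplement (curcumin or zinc), separately". It adds that "the maximum sample size was considered as the final sample size, which is sufficient to evaluate the main effects". It gives no interaction effect and no power for one.

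Statistical analysis compares the four groups by one-way ANOVA with LSD post hoc tests, or by Kruskal-Wallis, with ANCOVA if needed for confounders. No factorial model or interaction term is named. The objectives and the Hypothesis section do not mention synergy. The hypothesis is that co-supplementation improves the outcomes.

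**The concern.** In a 2 × 2 factorial, synergy between curcumin and zinc means that the combination does more than the sum of the two separate effects. That is the interaction, a difference of differences across all four cells. None of the pairwise LSD comparisons estimates it, and neither does Kruskal-Wallis.

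If each supplement works and the effects simply add, the combination should beat double placebo with no synergy at all. With the stated analysis, a significant result for that pair could be set beside the synergy wording and read as confirming it. A non-significant interaction, if someone tested one afterwards, could equally be read as showing no synergy when the interval was too wide to say so.

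The abstract sentence reaches further in two ways. Progression to type 2 diabetes is not among the outcomes, and follow-up is 90 days. Both synergy sentences also bring in the weight-loss diet, but under Intervention every participant receives that diet, so no contrast in the trial can show synergy with it.

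**Working it through.** **Inputs (Sample size section).** Zinc: means +16 and +3, SDs 12.8 and 15.3. Curcumin: means 3.64 and −7.54, SDs 8.17 and 7. Two-sided α = 0.05, power 0.80, 10% loss, 21 recruited per group. The section prints no unit. I take mg/dl, the unit used for FPG in the inclusion criteria.

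**The plan's own figures.** n = (S₁² + S₂²)(1.96 + 0.842)² / (X̄₁ − X̄₂)².
- Curcumin: difference 11.18; (66.7 + 49.0) × 7.85 / 125.0 = 7.27, rounded up to 8.
- Zinc: difference 13; (163.8 + 234.1) × 7.85 / 169 = 18.48, rounded up to 19.

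Both match the article. The larger, 19 per cell, is the planned evaluable number.

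**Common SDs (root mean square).** Zinc √[(12.8² + 15.3²)/2] = 14.1. Curcumin √[(8.17² + 7²)/2] = 7.61.

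**Interaction.** I = (Zn/Cur − Cur/P.Zn) − (Zn/P.Cur − P.Zn/P.Cur), on absolute change in FPG. With n per cell and one SD, SE(I) = SD × √(4/n).

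Standard errors with the zinc SD and n = 19:
- Cell against cell (19 v 19), the contrast in the sizing formula: 14.1 × √(2/19) = 4.58.
- Pooled main effect (38 v 38): 14.1 × √(1/19) = 3.24.
- Interaction: 14.1 × √(4/19) = 6.47.

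The interaction SE is therefore twice that of a pooled main effect, and 1.41 times that of the contrast actually sized.

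**Precision and power at 19 per cell** (noncentral t, 4 × 18 = 72 df, critical value 1.99):

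| SD assumed in all cells | SE(I) | 95% CI half-width | Interaction | Power |
|---|---|---|---|---|
| 14.1 (zinc) | 6.47 | 12.9 | 13 (whole planned zinc effect) | 51% |
| 14.1 (zinc) | 6.47 | 12.9 | 6.5 (half of it) | 17% |
| 7.61 (curcumin) | 3.49 | 7.0 | 11.2 (whole planned curcumin effect) | 88% |
| 7.61 (curcumin) | 3.49 | 7.0 | 5.6 (half of it) | 35% |

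An interaction of 13 is large: a zinc effect of 13 without curcumin would become 26 with it. With the zinc SD, the interaction detectable with 80% power is 18.4. If all 21 per cell were retained, power for 13 would be 55%. Reaching 80% for 13 would take 4 × 14.1² × 7.85 / 13² ≈ 37 per cell.

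For comparison, at 19 per cell with the zinc SD, power for a difference of 13 is 79% cell against cell and 98% for the pooled main effect. The main-effect claim in Sample size stands.

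**The case against.** A reader might infer that the trial was built to claim synergy. The documents do not support that. The objectives, hypothesis and outcomes never name synergy or interaction. Both synergy sentences are hedged with may, and the article's main Discussion does not repeat the word. The hypothesis needs only the combination against double placebo, which is among the LSD comparisons. Sample size openly limits itself to main effects, and sizing a factorial trial that way is ordinary practice. All of this stands, and it narrows the point to a mismatch between wording and analysis.

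A reader might also infer that the interaction has only about an even chance of detection in general. That holds for the zinc SD and an interaction of 13. With the curcumin SD, from the same section, power for an interaction of 11.2 is 88%. The article plans no interaction size, so all four figures are benchmarks. ANCOVA could improve precision by an amount the article does not let one calculate.

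Because both sentences mention the diet, synergy may partly mean supplements with diet. That reading does not rescue the wording, since every arm receives the diet.

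Finally, an analysis plan not shown here might contain an interaction contrast, and one could be formed from a four-group model. But the article does state its between-group analysis, and the method it states is pairwise in a declared factorial.

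**Conclusion.** The point holds as a mismatch. Synergy is offered in the rationale and in the abstract's closing sentence, while the sizing covers each supplement separately and the stated analysis does not estimate the interaction that would show it. The main-effect questions and the stated hypothesis are unaffected.

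Power for an interaction as large as a whole planned single-supplement effect runs from 51% to 88%, depending on which of the article's two SDs applies. For half that effect it runs from 17% to 35%. These figures assume 19 evaluable per cell, one SD in all four cells, inputs in mg/dl, no gain from covariate adjustment, and additivity judged on absolute change in FPG. The zinc SD is the natural base case because it fixed the sample size, but the range should be shown.

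The abstract sentence on delaying diabetes cannot be supported by this trial under any of these assumptions.

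**What to change.** - **Statistical analysis:** use a two-factor model with curcumin, zinc and curcumin × zinc. Report the interaction with its 95% CI, labelled exploratory. Keep Zn/Cur versus double placebo as the named contrast for the stated hypothesis.
- **Sample size:** state that the trial is not powered for the interaction, and give the range above with its two SDs.
- **Background and rationale, and the abstract:** word them so that curcumin-zinc synergy is claimed only if the interaction CI excludes zero in the favourable direction.
- **Abstract, Discussion paragraph:** remove the sentence linking a synergic effect to delayed progression to type 2 diabetes.

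The cost is a more modest claim and a little extra analysis. Recruitment, sample size and measurements do not change. Since the article reports recruitment under way, the change should be dated and made before unblinding.

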#### Primary objective

The primary objective is to compare the mean changes in the serum levels of biochemical parameters (fasting plasma glucose (FPG), 2 h post-prandial (2hpp), HbA1c, serum insulin, insulin resistance (IR), insulin sensitivity (IS) %, beta cell function (BCF) %, TG, TC, LDL-C, high-density lipoprotein (HDL), very low-density lipoprotein (VLDL), total blood antioxidant capacity (TAC), malondialdehyde (MDA), serum zinc, urine zinc, serum interleukin-B (IL-1B), and high-sensitivity C-reactive protein (hs-CRP)) between the groups.

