## Method

### Study design

The flow chart of the study design and the schedule of enrollment, interventions, and assessments are shown in Figs. 1 and 2, respectively. The participant will be randomized in a 2 × 2 factorial design into four parallel treatment groups: (1) curcumin group (Cur/P.Zn), curcumin supplement + placebo for zinc; (2) zinc group (Zn/P.Cur), zinc supplement + placebo for curcumin; (3) zinc + curcumin group (Zn/Cur), zinc supplement + curcumin supplement; and (4) placebo group (P.Zn/P.Cur), placebo for curcumin and zinc. The follow-up duration will be 3 months (90 days).

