### Outcomes

The primary outcomes include serum levels of biochemistry parameters except ALT and AST. The secondary outcomes are ALT and AST, body composition, PA, BP, HRQOL, and dietary intake. The primary and secondary outcomes will be conducted at the baseline and the end of the study (day 90 after intervention) for all participants. Only adherence will be checked at the end of every month.

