### Laboratory investigations

Blood samples (12 ml) of all participants will be collected after 12 h of overnight fasting at the baseline and at the end of the study. The samples will be collected into two different tubes (in the tube without anticoagulant and in EDTA tubes) and centrifuged to obtain the serum or plasma. The serum samples (3 ml) will be stored at − 80 °C. The plasma and the remaining serum will be used to determine the FPG, 2hpp (glucose oxidase/peroxidase method, BioSystem, Spain), HbA1c (HPLC, TOSOH, Japan), TG (glycerol phosphate oxidase/peroxidase method, BioSystem, Spain), TC (cholesterol oxidase/peroxidase method, BioSystem, Spain), HDL-C (direct method, BioSystem, Spain), SOD (colorimetric (420 nm) method, ZellBio GmbH, Germany), TAC (colorimetric (570 nm) method, ZellBio GmbH, Germany), MDA (colorimetric (535 nm) method, ZellBio GmbH, Germany), ALT, AST (IFCC method, BioSystem, Spain), serum insulin (enzyme-linked immunosorbent assay (ELISA) kit, Monobind, USA), serum zinc (flame atomic absorption spectrometry method (Ziest Chem Diagnostics kit, Iran), serum IL-1B (human IL-1β (ELISA kit), BE58011, IBL, Hamburg, Germany), and serum hs-CRP )ELISA kit, EU59131, IBL, Hamburg, Germany). At least 1 ml of random urine specimen (the fasting state is not necessary for urine collection) will be taken at the baseline and at the end of the study for the measurement (urine zinc by flame atomic absorption spectrometry method (Ziest Chem Diagnostics kit, Iran; normal range 15–150 μg/dl). All biochemical tests except IL-1B, hs-CRP, SOD, TAC, and MDA will be conducted immediately after sampling.

The following formula will be used to calculate VLDL and LDL-C:
VLDL = TG (mg/dl)/5 (this formula is valid only when TG are ≤ 400 mg/day)LDL-C = TC (mg/dl) − HDL-c (mg/dl) − TG (mg/dl)/5; Friedewald formula [50].

The homeostasis model of assessment 2 (HOMA-2) calculator will be downloaded from the University of Oxford and used to calculate IR, S%, and BCF% (http://www.dtu.ox.ac.uk/).

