### Statistical analysis

Before statistical analysis, all data will be reviewed to check the accuracy and completeness. The primary analysis will be conducted on the intention-to-treat (ITT) population. Per-protocol (PP) and sensitivity analyses may be conducted as appropriate. The normality of data will be checked by the Kolmogorov-Smirnov test. The variables will be reported as mean ± SD or median (*Q*). The percentage changes for each variable will be separately reported and calculated by the following formula:
$$ \left[\left(E-B\right)/B\times 100\right], $$

where *E* and *B* are the end value and the baseline value of the variable, respectively.

According to the normality assumption, the significant changes between the groups will be assessed through a one-way analysis of variance (one-way ANOVA) with post hoc (LSD) analysis or Kruskal-Wallis. Changes from the baseline to post-intervention within the groups will be illustrated through a paired *t* test or Wilcoxon signed-rank test. The qualitative and quantitative variables in the two groups will be compared using the chi-square and *t* test, respectively. If necessary, the analysis of covariance (ANCOVA) will be used to control the potential confounding variables.

All analyses will be performed using a statistical software package (SPSS), version 22.0 (SPSS, Inc., Chicago, IL, USA), or NCSS2020. Statistical significance will be determined at *p* < 0.05.

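### Eighteen biochemical outcomes are all primary at p < 0.05 although the trial is sized on FPG alone, so the error rate for the primary family is far above 5%, and LSD with four arms adds to it

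*Protocol article*

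**What the plan says.** The Primary objective section states: "The primary objective is to compare the mean changes in the serum levels of biochemical parameters". It lists 18: FPG, 2hpp, HbA1c, insulin, IR, IS%, BCF%, TG, TC, LDL-C, HDL, VLDL, TAC, MDA, serum zinc, urine zinc, IL-1B and hs-CRP. The Outcomes section does not narrow this: "The primary outcomes include serum levels of biochemistry parameters except ALT and AST". On that wording SOD is a nineteenth, because it is assayed under Laboratory investigations and named among the antioxidant markers in the Discussion. The Primary objective list omits it.

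Participants are "randomized in a 2 × 2 factorial design into four parallel treatment groups". The Sample size section is based on "the ability to detect a mean effect of FPG between the supplement and placebo groups for each supplement (curcumin or zinc), separately", with alpha 0.05 and beta 0.2. The between-group analysis is "one-way analysis of variance (one-way ANOVA) with post hoc (LSD) analysis or Kruskal-Wallis", and "Statistical significance will be determined at *p* < 0.05". Laboratory investigations gives VLDL as a fixed fraction of triglycerides: "VLDL = TG (mg/dl)/5 (this formula is valid only when TG are" not above a stated limit.

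**The concern.** The sample size treats the trial as having one deciding variable, while the objectives and outcomes give it 18 or 19 of equal rank. Each is judged at 0.05. Nothing says which outcome, how many of them, or which contrast between arms would support the Hypothesis section, which predicts significant improvement across the biochemical parameters. A single nominally significant marker could then be reported as a positive primary result, at an error rate well above the 5% used for sizing.

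The list also contains entries that add no separate evidence of benefit. VLDL is TG divided by 5, so its test repeats the TG test. Serum and urine zinc in a trial that gives zinc mainly show that zinc was taken. A rise in either would count as primary success without any metabolic improvement.

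**Working it through.** **1. The plan's own sample size.** The inputs are those in the Sample size section, and the formula is n = (S1² + S2²)(z0.975 + z0.80)² / (difference)², with (z0.975 + z0.80)² = 7.849.
- Curcumin: (8.17² + 7²) × 7.849 / 11.18² = 115.75 × 7.849 / 124.99 = 7.27, giving 8.
- Zinc: (12.8² + 15.3²) × 7.849 / 13² = 397.93 × 7.849 / 169 = 18.48, giving 19.

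Both match the article. The arithmetic is right, but it covers FPG only, at 0.05.

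**2. Chance of at least one significant primary outcome if nothing works.** There is one ANOVA per outcome at 0.05.
- Independent outcomes: 1 − 0.95^18 = 60.3%. With SOD added (19), 62.3%. With VLDL dropped as a repeat of TG (17), 58.2%.
- Correlated outcomes: the article gives no correlations, so these are assumed. Simulating 18 equally correlated normal outcomes in four arms of 19 (20,000 runs) gives about 48% at r = 0.4 and 36% at r = 0.6. Further simulation gave about 30% at r = 0.7. With correlation 0.5 or 0.7 within a domain and 0.1 between domains, and VLDL set equal to TG, it gave 52% or 45%.
- Leaving out VLDL, serum zinc and urine zinc (15 left): 1 − 0.95^15 = 53.7% if independent. Leaving out one HOMA-2 index as well (14 left): 51% if independent, about 41% at r = 0.4 and 31% at r = 0.6.

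**3. LSD within one outcome.** Four arms of 19 leave 4 × 18 = 72 error degrees of freedom, and t0.975 = 1.993. Suppose three arms are equal and the fourth differs enough for the ANOVA to be significant. LSD then compares the three equal arms with no further protection. The chance that their studentized range exceeds 1.993 × √2 = 2.819 is 12.1%.

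**4. Power with FPG as the only primary outcome.** On the zinc figures the SD is √(397.93/2) = 14.11. The difference is 13, and a factorial main effect compares 38 with 38 (two arms of 19 on each side).
- SE = 14.11 × √(2/38) = 3.236, and 13/3.236 = 4.017.
- At alpha 0.025: Φ(4.017 − 2.241) = Φ(1.776) = 96%.
- At 0.05/3 = 0.0167, Holm's first step with three contrasts: Φ(4.017 − 2.394) = Φ(1.623) = 95%.

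For a combination-versus-placebo contrast of the same 13 units (19 versus 19), SE = 14.11 × √(2/19) = 4.576 and 13/4.576 = 2.841. At 0.0167 this gives Φ(2.841 − 2.394) = Φ(0.447) = 67%. For an interaction of 13 units, SE = 14.11 × √(4/19) = 6.472 and 13/6.472 = 2.009, giving Φ(2.009 − 2.394) = Φ(−0.385) = 35%.

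**5. Keeping all 18 as primary with Bonferroni.** Alpha is 0.05/18 = 0.00278. Power for the 13-unit zinc contrast falls from 81% to 44% at 19 per arm. Restoring 80% needs 35 per arm, or 39 after 10% loss (156 in total).

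**The case against.** The best defence is that this is a condensed article, and that an order of testing or an adjustment across outcomes may sit in a full protocol or analysis plan that is not shown. That is fair for a mere absence, and the absence is not the point here. The article itself fixes the primary set, the threshold and LSD. A later plan could not single out one primary outcome without departing from the Primary objective and Outcomes sections.

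Several stronger readings should be resisted.
- A reader might infer that a false positive is more likely than not. The 60% figure needs 18 independent outcomes and no true effect. The overlap within the list argues against independence, and moderate common correlation takes the figure below one half.
- A reader might count six pairs on each of 18 outcomes, 108 tests, with 20% error per outcome. That assumes LSD is read without a significant ANOVA. The text calls LSD post hoc, which most naturally means after the ANOVA, and with that gate the error is about 5% per outcome when all four arms are equal. LSD also belongs only to the normal-theory branch; no pairwise method is named after Kruskal-Wallis. The 12% figure is the fair criticism.
- A significant zinc level should not be called a false positive. A real change is expected in the zinc arms; the trouble is that it would be a hollow success.
- IR and IS% might be taken as one quantity stated twice. The article says only that a HOMA-2 calculator supplies both, so the point does not rely on it.

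The SOD mismatch is a listing inconsistency and adds little to the multiplicity argument. The Discussion hopes to pave the way for a larger trial, which softens the consequences but does not change what this trial may claim as its primary finding.

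**Conclusion.** The concern holds. With 18 primary outcomes (19 counting SOD), each at 0.05, and sizing on one of them, the chance of at least one significant primary outcome when nothing works is 60% under independence and about 36% to 48% at common correlations of 0.6 to 0.4. It stays near 30% even at 0.7. The correlations are assumptions, but every case examined is at least six times the nominal 5%. Separately, ANOVA-gated LSD does not hold 5% with four arms once one arm truly differs; its error is then about 12% within that outcome. Neither figure depends on the sample size arithmetic, which reproduces.

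**What to change.** By a dated amendment before unblinding:
- Name change in FPG at day 90, the sizing variable, as the only primary outcome.
- State its contrasts in advance and control alpha over them, for example by Holm. They should be the two factorial main effects and, because the Background and Hypothesis sections centre on co-supplementation, either combination versus placebo or the interaction.
- Make the other markers secondary or exploratory, with SOD listed. Treat serum and urine zinc as exposure markers, and do not count VLDL as evidence separate from TG.
- If all-pairs comparisons are kept, use Tukey instead of LSD.
- Align the Primary objective, Outcomes and Statistical analysis sections, and the registry entry where it differs.

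The costs are that fewer outcomes can be called primary, and that the amendment falls while recruitment is under way according to Trial status. No added patients are needed for the main effects: power is about 96% at alpha 0.025, or 95% at 0.0167 with three contrasts, on the plan's zinc figures and assuming no interaction. That assumption sits uneasily with the synergy proposed in the Background, so it should be stated. The third contrast is weaker at the same 13-unit size, at 67% for combination versus placebo and 35% for interaction at 0.0167, and the amendment should say so.
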